#### Patient management

In the CLEVER study, all eligible patients are presented at a weekly multidisciplinary tumor board meeting. Decisions regarding neoadjuvant therapy versus upfront surgery are made by consensus based on published authoritative guidelines, taking into account tumor stage (II–IIIA generally considered for neoadjuvant), resectability, and patient preference. Once the treatment plan is determined, research staff obtain written informed consent from participants in the hospital room. The following two questions are explained in detail to ensure that patients fully understand. First, this study involves repeated blood sampling of eight scheduled time points over two years. Potential risks (*e.g*., transient pain, bruising, hematoma, infection) are described, and standard phlebotomy precautions are assured. Second, this study involves a two-year follow-up schedule, including clinical visits and imaging studies. Patients are informed of data confidentiality measures and their right to withdraw at any time without affecting clinical care. Patients treated with direct surgical resection belongs to the Naïve cohort while those undergoing surgical resection following neoadjuvant immunotherapy belongs to the Neoadjuvant cohort). For patients assigned to the neoadjuvant cohort, the consent form includes additional sections that explain the risk and benefit from the neoadjuvant therapies. Participants have the opportunity to ask questions and are provided contact information for study coordinators and the ethics committee. Comprehensive clinical information is collected from all participants, including age, gender, smoking history, radiological image characteristics, and histopathology descriptions.

### Sample collection

#### Tissue samples

In order to accurately sample and record the position, we have developed a standardized multi-region sampling process. Initially, the surgical sample is dissected along its maximum diameter. Equal-sized samples are then taken from one side of the tumor using a skin perforator. For smaller tumors, consider sampling from various locations on the opposite side. Samples from at least two tumor regions must be separated by 0.3 cm to 1 cm, depending on the tumor size, for inclusion in the study. Border samples should be collected at the interface between tumor and normal tissue to ensure that both tumor and normal samples are obtained. Paired normal tissue samples should be taken at least 2 cm away from the tumor edge. Last but not least, the central coordinates of each sampling point were recorded using a double-scale square and documented with photographs.

All tissue samples must be immediately placed into freezing tubes for preservation at -80°C. If the tumor is sufficiently large, a set of paraffin-embedded samples should also be collected for all tissues.

#### Blood samples

Participants in the study will have their blood drawn at eight prespecified time points: pre-surgery, 3 days after surgery, 1 month after surgery, 3 months after surgery, 6 months after surgery, 12 months after surgery, 18 months after surgery, and 24 months after surgery. Preoperative blood is collected on the morning of the surgery, while postoperative blood is collected according to the study design time points. As the follow-up blood collection time may have a time deviation from the set blood collection point, when recording the blood collection follow-up, we will truthfully record the blood collection time of that day and further calculate which time point the blood sample belongs to. We allow a maximum deviation of ± 1 month around each scheduled postoperative draw to accommodate clinical logistics. Sensitivity analyses will be performed by excluding samples collected outside the ± 2-week window and re-estimating MRD dynamics and their correlation with outcomes, to confirm the robustness of temporal patterns. For patients receiving neoadjuvant therapy, blood samples will also be taken on the first day of each course of treatment.

Peripheral blood samples, approximately 20 mL each, are collected into Cell-Free DNA BCT tubes (Streck, Omaha, USA) and transported to the laboratory. Plasma and white cell samples are separated according to the provided instructions within 24 h and stored at -80°C.

### Data collection and management

According to the medical record numbers of enrolled patients, clinical, imaging, and pathological data were completely, correctly, and clearly entered into the statistical information table through medical record inquiry. Clinical data are archived and stored as a database in numbered order, with multiple backups to ensure proper storage. The original files are retained for the period specified by relevant guidelines. Original data are managed by designated personnel and stored on the hospital’s internal computer hard disk, which is not accessible from external networks. The final archived data of this study are stored only in serial numbers and do not contain any personal privacy information of patients. No patient privacy information was involved when the data were used for publication.

## Multi-omics profiling

### Nucleic acid extraction

Genomic DNA and total RNA are purified from the frozen tumor and normal tissues using the AllPrep DNA/RNA Mini Kit (Qiagen, Hilden, Germany). DNA in paired white cell samples is extracted using the TIANamp Genomic DNA Kit (Tiangen, Beijing, China). Cell-free DNA in the plasma samples is extracted using the QIAamp Circulating Nucleic Acid Kit (Qiagen, Hilden, Germany). Nucleic acid concentrations are quantified using either the Qubit HS dsDNA Kit or the Qubit RNA HS Assay Kit (Invitrogen, Carlsbad, USA).

### Whole exome sequencing and analysis

The DNA library is prepared with an input of 200 ng genomic DNA using the VAHTS Universal Plus DNA Library Prep Kit for Illumina V2. The subsequent hybridization capture is performed using the SureSelect XT target enrichment system. The final DNA library is quantified using the Qubit 3.0 and fragment detection is conducted with the Agilent 2100. Finally, the DNA library is sequenced using paired-end 150 bp reads on the Illumina NovaSeq 6000 platform.

The sequencing data is analyzed using the WES pipeline. The sequencing data from white cells is used to exclude germline mutations. Clean reads in FASTQ format are aligned to the human UCSC reference genome (hg19/GRCh37) using the Burrows-Wheeler Aligner (BWA, v0.7.15). Sambamba (v0.6.8) is used to process PCR duplicates in the mapped BAM files. The Genome Analysis Toolkit (GATK v4.0.11.0) is employed for local realignment and base quality recalibration to compute sequencing coverage and depth. Single nucleotide variations (SNVs) and small insertions and deletions (Indels: < 50 bp) are identified using GATK MuTect2 (v1.1.4). Multiple testing correction for gene-level mutation frequency comparisons will be performed using the Benjamini-Hochberg procedure, with an adjusted p-value (FDR) cutoff of < 0.05.

Based on multi-region sequencing, region-based tumor mutation calling is combined to recall tumor-informed mutations, allowing for the acquisition of new recalled mutations for each region. Using these recalled region-level mutations, the phylogenetic tree is reconstructed using the CNIPHER method,^[24]^ enabling the identification of clonal and subclonal mutations. Somatic copy number alterations (SCNAs) are processed using ASCAT (V2.3), which allows for the determination of intratumoral heterogeneity in both SNVs and SCNAs, specifically assessing subclonal mutation fractions and subclonal SCNAs fractions. This comprehensive analysis facilitates a deep understanding of evolutionary events within the tumor, characterized by intratumoral heterogeneity, clonal illusion, subclonal expansion, whole genome doubling, weighted genome integrity index (wGII), and loss of heterozygosity (LOH). These insights provide a detailed depiction of the tumor’s evolutionary landscape and its underlying genetic dynamics.

### RNA sequencing and analysis

To construct a transcriptome sequencing library, 1–3 μg of total RNA is prepared using the VAHTS Universal V6 RNA-Seq Library Prep Kit for Illumina (NR604-01/02). The final RNA library is quantified using the Qubit 3.0, and fragment analysis is conducted with the Agilent 2100. Additionally, the Bio-RAD CFX 96 fluorescence quantitative PCR is used to quantify the effective concentration of the RNA library (ensuring it is greater than 10 nmol/L) using the Bio-RAD KIT iQ SYBR Green. The RNA library is then sequenced using paired-end 150 bp reads on the Illumina NovaSeq 6000 platform.

The sequencing data is aligned to the human UCSC reference genome (hg19/GRCh37) using the STAR aligner (version 2.7.4a) and annotated with ANNOVAR software. Subsequent analyses include immune cell infiltration assessment, identification of differentially expressed genes (DEGs), enrichment analysis, and subtypes clustering. DEGs will be identified with DESeq2, applying the Benjamini–Hochberg FDR correction. Genes with FDR < 0.05 and |log₂FoldChange| > 1 will be considered significant. These analyses aim to explore the heterogeneous tumor microenvironment, providing insights into the complex interactions and variations within the tumor.

### Single-cell RNA-seq sequencing

Fresh or frozen tissue samples are enzymatically digested to obtain single-cell suspensions, achieving a concentration of 700–1200 living cells per ml. Libraries are prepared using the Chromium Next GEM Single Cell 3’ Reagent Kits v3.1, following the manufacturer’s protocol. The purified library is sequenced on the Illumina NovaSeq 6000 platform with a sequencing length of 150 bases in a paired-end format.

The resulting FASTQ files are processed and quantified using the GRCh38 human reference genome with the Cell Ranger single-cell toolkit (v.3.1.0). Quality control steps include filtering out: (1) low-quality cells expressing < 200 genes; (2) > 25,000 or < 500 UMIs; (3) Low-quality cells with > 20% mitochondrial gene count; (4) Cells judged as twin by DoubletFinder. All samples were integrated using the Seurat or Seurat-wrappers package (v0.1.0). Raw counts were normalized with a scale factor of 10,000 per cell and subsequently log-transformed (log [count+1]). The top 2000 highly variable genes (HVGs) were identified for integration purposes. Data scaling and principal component analysis (PCA) were conducted using default settings. Significant principal components (PCs) were selected based on the elbow plot of the standard deviations of the PCs and were utilized for neighbor detection, followed by Louvain clustering ^[25]^ and uniform manifold approximation and projection (UMAP).^[26]^ The same analytical pipeline was applied for the detection of sub-clusters.

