### Spatial enhanced resolution omics-sequencing (stereo-seq)

The tissue was embedded in an OCT embedding agent (Sakura, 4583) and stored at -80°C. It was then sectioned into 10 μm thick slices using a cryotome (Leica, CM1950). Tissue structure was identified through H & E staining. Appropriately sized sections were placed on the Stereo-seq chip, and tissue integrity was assessed using ssDNA staining (Invitrogen, Q10212). Following the manufacturer’s protocol, chip permeation, RNA capture, reverse transcription, and cDNA library construction were completed.

Spatial transcriptome data were processed using Spaceranger (v.1.2.2). To achieve spatial localization of cell subsets on the spatial transcriptomics (ST) slides, we integrated the Stereo-seq data with single-cell RNA sequencing (scRNA-seq) data using the Seurat package. Seurat estimated the expression abundance of each cell subset at each spatial location by analyzing the similarity of expression patterns, thereby mapping the complete spatial distribution of cell types. These results are suitable for downstream analysis.

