## Data analyses

### Multi-omics data integration

For the CLEVER cohort, we implemented a multidimensional profiling strategy encompassing three complementary analytical axes: molecular stratification (genomic whole-exome sequencing, transcriptomic RNA-seq, and proteomic GeoMx DSP protein), resolution scaling (bulk tissue analysis, single-cell resolution, and spatial mapping), and cross-platform integration. This framework was operationalized through molecularly barcoded aliquots derived from identical tumor regions, ensuring cellular and spatial concordance across omics layers.

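### The tissue rule sends every sample straight to -80°C, while single-cell sequencing digests fresh or frozen tissue to living cells and pools all samples without regard to input type

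*Protocol article*

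**What the plan says.** The section Tissue samples (under Sample collection) gives one storage rule: "All tissue samples must be immediately placed into freezing tubes for preservation at -80°C". It makes one addition: "If the tumor is sufficiently large, a set of paraffin-embedded samples should also be collected for all tissues". It mentions no fresh aliquot and names no freezing medium.

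The section Single-cell RNA-seq sequencing starts from a different premise: "Fresh or frozen tissue samples are enzymatically digested to obtain single-cell suspensions", "achieving a concentration of 700–1200 living cells per ml". Fresh and frozen tissue share one enzymatic route. One filter set then applies to every cell: fewer than 200 genes, fewer than 500 or more than 25,000 UMIs, doublets, and "Low-quality cells with > 20% mitochondrial gene count". All samples are integrated together with Seurat tools, and input type is not mentioned.

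The Stereo-seq section describes another handling route: "The tissue was embedded in an OCT embedding agent (Sakura, 4583) and stored at -80°C". The section Multi-omics data integration claims matched material across assays: "This framework was operationalized through molecularly barcoded aliquots derived from identical tumor regions, ensuring cellular and spatial concordance across omics layers".

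**The concern.** Staff cannot follow both sections as written. If the storage rule is kept, no fresh tissue is available for digestion. If fresh tissue is digested, the storage rule has been broken for those samples. If frozen tissue is digested, nothing in the text explains how cells stay alive through storage.

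The statistical issue follows from the words fresh or frozen. The plan allows two input types and treats them as one. If handling changes which cells survive to be sequenced, cell-type proportions will depend partly on handling. The single-cell data are also the reference for placing cell types on Stereo-seq sections and for inferring cell-type proportions in GeoMx regions (ScRNA-seq + Spatial Transcriptomics), so a handling effect there would not stay in one assay. Describing the microenvironment under neoadjuvant therapy is a stated aim. If the mix of fresh and frozen input differed between the naïve and neoadjuvant cohorts, handling and treatment could not be told apart.

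**Working it through.** The plan gives no figure to reproduce on this point, and no power or error rate enters it. The check is a comparison of sections, with a short identity for the batch effect and one arithmetic check on the unit.

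**1. Input material.** Tissue samples: all tissue, immediately, to -80°C, plus paraffin where the tumour is large enough. Single-cell section: fresh tissue or frozen tissue. The fresh input falls outside the storage rule and its single addition. This is a direct conflict.

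**2. Living cells from frozen tissue.** The single-cell section sets a living-cell target for both inputs. Neither section describes viable freezing or a separate route for frozen tissue. The supportable conclusion is that the text does not secure the target for frozen tissue, not that the target is impossible.

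**3. What later steps can remove.** The filters act on cells that reached sequencing. Integration aligns expression profiles among those cells. Neither can restore cells lost before sequencing. Confounding bias correction uses age, sex, smoking status, clinical stage and ECOG performance status. These describe the patient, not the aliquot, so matching or adjusting on them leaves a handling difference in place. By contrast, the section Blood samples does plan for handling variation: it sets a ±1 month window and a sensitivity analysis excluding samples outside ±2 weeks.

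**4. Form of the possible bias.** Let a cell type have true proportion *p* in every tumour, and let freezing change its recovery by a factor *r* relative to the other cell types.

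- Expected proportion in a fresh sample: *p*
- Expected proportion in a frozen sample: *p′* = *pr* / (*pr* + 1 − *p*)
- Mean in a cohort with frozen share *f*: *f p′* + (1 − *f*) *p*
- Spurious difference between cohorts A and B: (*f*_A − *f*_B)(*p′* − *p*)

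The last line is zero if *r* = 1 or if the two cohorts have the same frozen share. The article gives no value for *r* or *f*, so the bias can be described but not sized. Equal frozen shares remove the cohort contrast, but the pooled reference still carries the average distortion *f*(*p′* − *p*).

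**5. The concentration unit.** Cells loaded = concentration × volume. The article does not give a load volume, so it is assumed here.

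| Assumed load | At 700 per ml | At 1200 per ml |
|---|---|---|
| 0.02 ml | 14 | 24 |
| 0.05 ml | 35 | 60 |
| 0.1 ml | 70 | 120 |

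Even a full millilitre holds only 700 to 1200 cells, yet the section goes on to cluster and sub-cluster cells. The unit is probably a misprint.

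**The case against.** The best defence is that the storage sentence is a general banking rule, not a complete handling list. The OCT embedding in the Stereo-seq section is a route that sentence does not mention, the integration section refers to aliquots, and the single-cell section names its own input. A condensed article may also leave freezing medium and dissociation details to a fuller protocol or laboratory procedure that is not shown. This stands to the extent that the missing medium is not in itself a fault. It does not remove the conflict, because the article does state a rule covering all tissue, names one addition, and then uses an input outside both.

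A reader might infer more: that no stored sample can yield the measurement, or that fresh and frozen runs are not comparable. The documents support neither. The first assumes plain freezing without a protectant, which the storage sentence does not say, and it overlooks that fresh tissue is allowed. The second is stated nowhere and shown nowhere; what can be said is that a batch effect is possible and unhandled.

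It is also fair that confounding with cohort is hypothetical. Nothing shows that input type differs between cohorts, and no specific naïve-versus-neoadjuvant test on single-cell proportions is written down. The unit slip is editorial, since library preparation follows the manufacturer's instructions.

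**Conclusion.** The conflict between the storage rule and the single-cell input is established from the text. So is the lack of any provision for input type in the single-cell analysis, although mixed input is expressly allowed. The consequence is conditional: a handling batch effect in cell-type composition arises only if recovery differs by input type, and it biases a cohort contrast only if the mix of inputs also differs by cohort. Its size is unknown.

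The reach is limited to the single-cell results and the spatial estimates that use them as reference. Two-year DFS and OS, the sample size, and the exome, bulk RNA and MRD work do not depend on it. The point deserves attention now because input type cannot be changed once tissue is stored, and recruitment began in April 2022.

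**What to change.** - Reconcile the two sections: state which aliquots for single-cell work are exempt from the -80°C rule, or how they are frozen so that cells stay viable.
- Record input type (fresh or frozen) for every single-cell sample and report it by cohort.
- Check the quality filters separately by input type: cells removed by each filter, and the mitochondrial and UMI distributions.
- Stratify by or adjust for input type in every comparison of cell composition, including naïve versus neoadjuvant.
- Add a sensitivity analysis restricted to one input type, and repeat the Stereo-seq mapping and GeoMx deconvolution with that restricted reference.
- Correct the per-ml unit as an editorial matter.

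The cost is a few sentences, one extra field per sample and a little more analysis. The real downside is smaller strata, and so less precise composition estimates, especially if one input type is rare.

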### Spatial enhanced resolution omics-sequencing (stereo-seq)

The tissue was embedded in an OCT embedding agent (Sakura, 4583) and stored at -80°C. It was then sectioned into 10 μm thick slices using a cryotome (Leica, CM1950). Tissue structure was identified through H & E staining. Appropriately sized sections were placed on the Stereo-seq chip, and tissue integrity was assessed using ssDNA staining (Invitrogen, Q10212). Following the manufacturer’s protocol, chip permeation, RNA capture, reverse transcription, and cDNA library construction were completed.

Spatial transcriptome data were processed using Spaceranger (v.1.2.2). To achieve spatial localization of cell subsets on the spatial transcriptomics (ST) slides, we integrated the Stereo-seq data with single-cell RNA sequencing (scRNA-seq) data using the Seurat package. Seurat estimated the expression abundance of each cell subset at each spatial location by analyzing the similarity of expression patterns, thereby mapping the complete spatial distribution of cell types. These results are suitable for downstream analysis.

### GeoMx digital spatial profiling

A whole transcriptome atlas comprising 18,000 genes and a proteome atlas consisting of 570 proteins were generated using the GeoMx Digital Spatial Profiler (NanoString) on formalin-fixed, paraffin-embedded (FFPE) tissue sections. The slides were stained with morphological markers, including PanCK (epithelial cell marker), CD3 (lymphocyte marker), CD68 (macrophage marker), and DAPI (DNA marker). Based on these markers, 178 circular and polygonal regions of interest (ROIs), along with two negative controls, were selected for analysis.

Digital counts for each gene were standardized following quality control procedures. Protein digital counts were normalized using internal spike-in controls (ERCC) and the signal-to-noise ratio (SNR). DESeq-based differential expression analyses for both transcript and protein counts will include FDR control *via* the Benjamini–Hochberg method, reporting only targets with adjusted p-values < 0.05 as significant.

### Imaging mass cytometry

The paraffin-embedded tissues were sectioned into 4 μm slices and heated at 68°C for 1 h. The slices underwent dewaxing twice in xylene, followed by rehydration through a graded series of ethanol solutions at concentrations of 95%, 85%, and 75%. Antigen retrieval was conducted by heating the slices at 100°C for 30 min, followed by natural cooling. Subsequently, the slices were washed twice with PBS-TB for 5 min each and then blocked with SuperBlock for 30 min. After blocking, the slices were washed three additional times with PBS-TB and incubated overnight at 4°C with a metal-labeled antibody cocktail (Maxpar® X8 Kit). Post-incubation, the slices were washed and treated with 1.25 μmol/L Intercalator-Ir in PBS-TB at room temperature for 30 min, followed by washes with PBS-TB and distilled water. The prepared sections were then scanned using a Hyperion Imaging System to generate multiple images.

The IMC data processing involved four steps: overflow compensation, image denoising, contrast enhancement, and cell segmentation. The range of label expression was normalized to the 99th percentile for each channel, and batch effects were corrected using Harmony (v0.1.0). Clustering of cells was performed using Rphenograph (v0.99.1) with 100 nearest neighbors, and the cluster means were visualized as an annotated heat map.^[27]^ The K-means clustering method with (k = 15) was employed to identify cell neighborhoods (CNs) using a clustering window of the 20 nearest cells, based on Euclidean distance. Cell-cell interactions were analyzed using an arrangement assay facilitated by the imcRtools package (v1.0.2).^[28]^

